#### Health related quality of life (HRQoL)

The values on the EORTC QLQ-C30 subscales will be calculated and transformed to 100-points scales according to guidelines. The two subscales of the HAD-scale will be calculated as in the original publication, and suggested cut-offs will be implemented, making it possible to compare proportions of patients using the Chi2-test. HRQoL will be analyzed by linear regression models, including both randomization arms and adjusted for sex, age and baseline values for the studied scales.

Only persons at the main study center with defined roles will have access to the final trial data set.

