### Secondary endpoints

The secondary endpoints are survival from diagnosis of relapse and health related quality of life (HRQoL).

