### Questionnaires

The EORTC Quality of Life Core Questionnaire (EORTC QLQ-C30), Version 3 is a cancer-specific questionnaire consisting of 30 items including five functional scales (physical-, role-, emotional-, cognitive-, and social functioning), three multi-item symptom scales (fatigue, pain, nausea and vomiting), five single items (dyspnea, loss of appetite, constipation, insomnia, diarrhea, financial difficulties related to the disease) and a global quality of life scale [22]. The responses are scored with 4-point scales ranging from 1 (“Not at all) to 4 (“Very much”), with the exception of the two items assessing global quality of life which are scored on a 7-point scale ranging from 1 (“Very poor”) to 7 (“Excellent”). The time frame is “during the previous week”. Reference values from the Swedish population are available [23].

The Hospital Anxiety and Depression Scale (HAD-scale) is developed to assess anxiety and depressive symptoms in somatically ill patients [24]. It consists of 14 items, 7 assessing anxiety (HAD- A) and 7 assessing depression (HAD-D). The presence of problems during the preceding week is rated on a four- graded scale from 0 (“No problem”) to 3. The scores for each subscale are summed, giving a maximum of 21. Two cut-off points have been suggested: 0–7 no problems of clinical relevance (non-cases), 8–10 cases that warrant further psychiatric investigation (possible cases), and ≥ 11 clinical levels of anxiety/depression (probable cases). The HAD-scale has been widely used and the Swedish version has been validated in patients with CMM [25] and in breast cancer patients [26].

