### Statistical considerations

The sample size is based on the primary endpoint OS at 5 years.

Based on data from the Swedish Melanoma Registry, the following numbers of patients diagnosed and classified according to AJCC7 (version 7) are expected:
Stage IIB-C: 325 patients/year with a risk of recurrence during the first 3 years of 20–30%.Stage III: 350 patients/year with a risk of recurrence during the first 3 years of 50–60%.

The 5-year mortality for the entire group is estimated at 40% and we aim to detect a difference in hazard ratio for death of at least 20%. With a risk of type 1 error of 5% and type 2 error of 15%, 573 patients should be randomized to each group. With an expected dropout rate of about 10%, the planned number of randomized patients should be 1300.

However, with the introduction of systemic adjuvant treatment for stage IIIB-D patients in early 2019, less relapses are expected to occur in this subgroup. Impressive long time results for systemic treatments in advanced disease have also been presented [27, 28]. Hence, more patients than originally planned need to be included to meet the statistical requirements. Therefore, updated power calculations taking these factors into consideration are planned when final OS results for the pivotal adjuvant studies (COMBI-AD, CheckMate 238 and KEYNOTE-054) have been compiled (www.clinicaltrials.gov; NCT01682083, NCT02388906 and NCT02362594). Since the final OS analysis for the COMBI-AD study is planned in the end of 2021, the final OS results of CheckMate 238 will most likely also be presented next year and the final OS analysis for the Keynote-54 study is expected in less than three years, we plan to conduct new power calculations in autumn 2023. We expect that patient recruitment has not ended by then.

Results will be evaluated both on an intention-to-treat basis and per protocol. Patients who withdraw their informed consent remain in their allocation group when evaluated on the intention-to-treat basis, and are excluded when evaluated on the fulfilled protocol basis.

Survival data will be analyzed according to the Kaplan-Meier method and comparison between groups will be performed with the log-rank method. Binominal data will be analyzed with Chi-square statistics and continuous data with Mann-Whitney U test. Level of significance two-sided *p* < 0.05.

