### Ethical considerations

Patients in both groups will receive follow-up according to standard of care in Sweden today. Thus, we consider there is no risk for inadequate care by inclusion in the TRIM study. All participants must give written informed consent for participation. This can be withdrawn at any time. Patients declining to participate or who withdraw from the study will be followed according to the national guidelines i.e. the same follow-up as the study control group. The principles in the Declaration of Helsinki will be met.

It is uncertain whether imaging during follow-up is of benefit for the patients. The imaging examination schedule in this study is unlikely to harm the individual patient, although the radiation dose should not be neglected.

A negative impact on the patient’s well-being in the waiting period after the imaging examination, before he/she is informed of the results, cannot be ruled out. Furthermore, inconclusive imaging results, sometimes leading to further investigations, i.e. biopsies and/or a repeated imaging examination are likely to cause distress and reduced HRQoL. Therefore, we consider it important to assess the impact of the follow-up procedures in the TRIM-study.

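### HRQoL is tested at one blanket 0.05 level with no lead scale or time: up to 68 contrasts, about 3.4 chance findings expected, and a chance of at least one of roughly 33% to 97%

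*Protocol article*

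**What the plan says.** - **Endpoint.** Protocol article, Secondary endpoints: "The secondary endpoints are survival from diagnosis of relapse and health related quality of life (HRQoL"). No scale or time point is attached.
- **Scales.** Questionnaires lists for the QLQ-C30 "five functional scales (physical-, role-, emotional-, cognitive-, and social functioning), three multi-item symptom scales (fatigue, pain, nausea and vomiting"), then "five single items (dyspnea, loss of appetite, constipation, insomnia, diarrhea, financial difficulties related to the disease) and a global quality of life scale". The HAD scale adds an anxiety and a depression subscale, with two suggested cut-offs.
- **Times.** The HRQoL section under Methods and Table 1 give baseline and months 12, 21, 24 and 36. Month 21 is completed at home, and the others at study visits.
- **Analysis.** The HRQoL part of Statistical considerations says "HRQoL will be analyzed by linear regression models, including both randomization arms and adjusted for sex, age and baseline values for the studied scales". For HAD, cut-offs are also applied, "making it possible to compare proportions of patients using the Chi2-test".
- **Error level.** Statistical considerations: "Level of significance two-sided *p* < 0.05". The same section plans both intention-to-treat and per-protocol evaluation.
- **Stratification.** Study procedure and randomization stratifies by tumor stage and imaging method. Neither is among the HRQoL covariates.
- **Early analysis.** The Discussion plans a first HRQoL analysis once 100 patients per arm have baseline and one-year data.
- **Motivation.** Ethical considerations names the worry: "A negative impact on the patient’s well-being in the waiting period after the imaging examination".

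**The concern.** Taken together, the stated rules allow many HRQoL comparisons, each judged at 0.05 and none ranked above another. The conclusion on HRQoL can then depend on which scale and month a report emphasises. A chance difference could be presented as harm from imaging or as reassurance. A real effect on anxiety, which is the effect the trial worries about, could be lost among 17 scales.

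Two stated choices add to this. HAD gets two analyses with no order between them, and the chi-square one makes no use of the baseline score. The regression leaves out the factors used to stratify randomization. The early analysis also matters for timing: a lead outcome named after a between-arm look would be chosen with data in hand. The article expects the trial to influence follow-up guidelines, so the HRQoL result will carry weight.

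**Working it through.** The article states no HRQoL error rate, power or sample size, so there is no HRQoL figure to reproduce.

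**1. Count of contrasts**
- QLQ-C30: 5 functional + 3 symptom + 6 single items + 1 global = 15. The text says five single items but names six; the list is used here.
- HAD: 2 subscales. Total 15 + 2 = 17.
- Follow-up times: 12, 21, 24 and 36 months = 4.
- Every scale at every time: 17 × 4 = 68. One test per scale: 17.
- HAD chi-square tests, with one cut-off: 2 × 4 = 8 more, giving 76.

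**2. Expected false positives under the global null**

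This is number of tests × 0.05, whatever the correlation.
- 68 × 0.05 = 3.4
- 17 × 0.05 = 0.85
- 76 × 0.05 = 3.8

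**3. Chance of at least one, if independent:** 1 − 0.95^k
- k = 68: 1 − 0.95^68 = 96.9%
- k = 17: 1 − 0.95^17 = 58.2%
- With 16 scales (five single items taken literally), k = 64: 96.2%

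**4. Chance of at least one, with correlation**

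The article gives no correlations. Assumption: exchangeable, 0 to 0.6 between scales and 0 to 0.7 between times. Results come from 100,000 simulated sets of null test statistics per setting, two-sided 0.05.

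| Between-scale correlation | 17 tests | 68 tests, between-time 0.5 | 68 tests, between-time 0.7 |
|---|---|---|---|
| 0 | 58% | 94% | 91% |
| 0.2 | 54% | 92% | 88% |
| 0.3 | 49% | 90% | 84% |
| 0.5 | 39% | 80% | 74% |
| 0.6 | 33% | 74% | 66% |

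The range is therefore 33% to 58% for one test per scale, and 66% to 97% for 68 tests (97% being full independence).

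**5. The early analysis.** It uses one follow-up visit, month 12. If it compares the arms on all scales there are 17 contrasts however the regression is set up, so the 33% to 58% range applies to that look alone.

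**6. What control would cost if nothing led.** Bonferroni levels would be 0.05/68 = 0.0007 or 0.05/17 = 0.0029. A single lead contrast keeps 0.05.

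**7. Covariates.** Randomization is stratified by stage and imaging method, while the regression uses sex, age and baseline. Leaving out stratification factors does not bias the arm comparison. It tends to make standard errors too large when those factors predict HRQoL.

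The second analysis set and the second HAD cut-off would add further overlapping tests, which are not counted here.

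**The case against.** The strongest reply is that this is a journal article condensing a full protocol (version 1.4), and a statistical analysis plan may exist. The lead scale, the lead time and the multiplicity rule for a secondary endpoint are commonly placed there. That stands: the bare absence of a multiplicity policy is not a fault of the article. What remains is what the article does fix: the covariates, a second HAD analysis with no stated rank, one blanket level and an early look.

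A reader might infer three stronger things, and the documents do not support them.

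- **That a significant HRQoL result is nearly certain by chance.** The 97% needs 68 independent tests. These are related scales repeated in the same patients, and under the assumed correlations the figure falls to as low as 66%, or 33% with one test per scale.
- **That separate regressions are planned at each visit.** The text does not say so. One longitudinal regression per scale fits the wording equally well. Nor does the article say that one significant scale will count as an HRQoL effect.
- **That dichotomising HAD discards half the information.** With z the normal cut point that leaves a proportion p of cases, the retained share is φ(z)²/[p(1 − p)]. For an assumed 20% case rate this is 0.280²/0.16 = 0.49, but the article gives no case rate. The loss also affects only the chi-square version, since HAD is analysed by adjusted regression too, and the wording on proportions is permissive.

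It is also fair to say that baseline-adjusted linear regression is a valid randomized comparison, that HAD includes a dedicated anxiety subscale, and that the sample size and its error rates were set for overall survival, which this point does not touch.

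**Conclusion.** The point holds in a moderate form. As stated, the HRQoL analysis allows up to 68 contrasts at 0.05 with none in the lead, and about 3.4 would be significant by chance if the arms did not differ. The chance of at least one lies between about 33% and 97%, well above 5% on every reading computed.

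The count rests on the scales as listed and the four scheduled times. The lower and upper ends rest on whether each scale is tested once or at every time, and on assumed correlations. Near-certainty of a false finding is not established. The point concerns a secondary endpoint only. It is worth correcting because the correction is cheap and because the choice of a lead outcome loses value once between-arm HRQoL data have been seen.

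**What to change.** Amend the HRQoL part of Statistical considerations as follows.

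1. **Model.** Use one repeated-measures model per scale over months 12, 21, 24 and 36, with arm, visit and arm-by-visit terms. Adjust for the baseline value, sex, age, tumor stage and imaging modality.
2. **Lead outcome.** Before any further between-arm HRQoL analysis, name one outcome and one contrast to be tested at two-sided 0.05. The HAD anxiety score is a natural candidate, since it matches the worry in Ethical considerations. The contrast needs thought: in Table 1, months 12, 24 and 36 coincide with scheduled imaging in the experimental arm and month 21 does not, so an average over all four times and a contrast at one time ask different questions.
3. **Other scales.** Report them with 95% confidence intervals, either as exploratory or under a stated adjustment such as Holm or false discovery rate.
4. **HAD cut-offs.** Present the proportions descriptively and state which cut-off is used.
5. **Early analysis.** If a between-arm look at 100 patients per arm has already taken place, say so and state whether the lead outcome was chosen before or after it.

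The cost is analysis wording only, with no new data or visits. The downside is that the remaining scales lose confirmatory status. If the full protocol or an analysis plan already fixes these items, a reference to it is enough for items 2 and 3.

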### Ethical considerations

Patients in both groups will receive follow-up according to standard of care in Sweden today. Thus, we consider there is no risk for inadequate care by inclusion in the TRIM study. All participants must give written informed consent for participation. This can be withdrawn at any time. Patients declining to participate or who withdraw from the study will be followed according to the national guidelines i.e. the same follow-up as the study control group. The principles in the Declaration of Helsinki will be met.

It is uncertain whether imaging during follow-up is of benefit for the patients. The imaging examination schedule in this study is unlikely to harm the individual patient, although the radiation dose should not be neglected.

A negative impact on the patient’s well-being in the waiting period after the imaging examination, before he/she is informed of the results, cannot be ruled out. Furthermore, inconclusive imaging results, sometimes leading to further investigations, i.e. biopsies and/or a repeated imaging examination are likely to cause distress and reduced HRQoL. Therefore, we consider it important to assess the impact of the follow-up procedures in the TRIM-study.

## Discussion

The incidence of CMM is rapidly increasing in many countries and hence the number of patients who will be subject to follow-up is growing. Follow-up programs usually aim to support and educate the patients and to improve outcome by earlier detection of recurrent disease, both locoregional and distant. Early detection of recurrence is proposed to be beneficial by increasing the chance of radical resection or enabling an early onset of systemic treatment. Due to lack of reliable data it is, however, unclear if scheduled follow-up visits lead to earlier detection of localized disease. One exception is when regional ultrasound is performed in patients with a positive SNB, but no benefit in survival was demonstrated [6]. In fact, the patients usually detect their relapses themselves despite regular controls [29].

In earlier studies the majority of relapses occurred during the first years after primary surgery, indicating that follow-up is most appropriate in the first few years after diagnosis. However, little is known about the potential OS benefit in finding recurrent metastatic disease early, not the least in the modern era with potent systemic melanoma treatments available. As a consequence, there are great variations between national guidelines regarding the recommendations for follow-up after surgery for high-risk CMM. An increasing number of countries have implemented whole-body FDG/PET-CT or CT at various frequencies and duration, as part of their routine follow-up programs in spite of lack of evidence from randomized studies. Intense follow-up programs require resources which are expensive and might negatively affect the patients´ HRQoL.

The importance of not introducing a more intense follow-up program based on mere assumptions of benefit is underlined by the results of the COLOFOL study. In this study, additional CT examinations after curative surgery for colorectal cancer did not result in a significant reduction in 5-year overall mortality or colorectal cancer–specific mortality [30].

In conclusion, the impacts of high-volume follow-up programs including imaging after radical surgery for CMM on OS are not sufficiently studied to create evidence-based guidelines. Despite this, the Current Oncological Practice (COP) is moving towards high intensity follow-up programs while a Minimal Acceptable Practice (MAP) might be just as good. It is therefore of uttermost importance to perform a large controlled trial, randomizing patients to control programs with or without imaging. The TRIM study aims to include at least 1300 patients and is the first randomized trial to investigate the potential benefit of imaging assessments as part of the follow-up program after radical surgery of CMM and to explore their impact on the patients´ HRQoL. A first HRQoL data analysis is planned when 100 patients in each study arm have completed baseline and first year HRQoL assessments which is expected in early spring 2021. The results of the TRIM study will most likely impact future guidelines for follow-up of high-risk CMM patients.

### Trial status

The first patient was recruited in June 2017. On the 2nd of October 2020, 564 patients had been recruited at 19 centers in Sweden as shown in Fig. 2. Three hundred and sixty-eight patients out of 564 were included at oncology sites. Recruitment is ongoing. Latest protocol version and date: 1.4, 2018-12-11.

**Fig. 2 Fig2:**
[figure not shown]
Recruitment status for individual centers. Striped bars represent university hospitals. Oncology sites are marked with a star (*)

The inclusion rate differs substantially between centers. One major reason is the large differences in target populations between centers. However, some centers have a large potential to recruit more patients and the various reasons for suboptimal inclusion rates are important to address for the study team. Obstacles so far have consisted of:
Long waiting times for pathology reports after wide excision +/− SNB results at some sites resulting in missing deadline for study inclusion. These waiting times have improved over time and to further diminish this problem, time from final surgery to possible study inclusion was extended from six to eight weeks.In some regions, stage II patients have not been discussed at a multidisciplinary conference and therefore, all surgeons have not referred these patients to the regional study center for study participation. This has improved and it is also possible to start up satellite centers.

Very few patients have declined participation in the TRIM study when offered to participate.

Strategies to improve adherence to the protocol, besides monitoring, include regular newsletters to the study centers and continuous support mainly by email.

## Data Availability

Not applicable since the trial is ongoing and no results are reported. The results of the study will be presented in future publications.

## Abbreviations

CMM: Cutaneous malignant melanoma
OS: Overall survival
SNB: Sentinel node biopsy
HRQoL: Health related quality of life
DFS: Disease free survival
